# Efficacy of Yokukansankachimpihange on sleep disturbance in Parkinson's disease

**DOI:** 10.1097/MD.0000000000011298

**Published:** 2018-06-29

**Keywords:** functional near-infrared spectroscopy, Parkinson's disease, polysomnography, protocol, sleep disturbance, Yokukansankachimpihange

## Abstract

**Introduction::**

Parkinson's disease (PD) is a progressive neurodegenerative disorder that includes motor and nonmotor symptoms. Sleep disturbance is known to decrease the quality of life in patients with PD, and there are limitations to the pharmacotherapy currently in use. Therefore, complementary treatment therapies are required to address these limitations. The traditional herbal medicines Yokukansan (YKS) and Yokukansankachimpihange (YKSCH) have been used to treat insomnia and night crying in children, suggesting their effectiveness against sleep disturbance in patients with PD. We will evaluate whether YKSCH improves sleep disturbance in PD and will identify YKS-related changes in hemodynamic parameters, and neurotransmitter and hormone levels in patients with PD experiencing sleep disturbance.

**Methods::**

We will conduct a randomized, double-blinded, placebo-controlled parallel trial in 34 patients with PD and sleep disturbance, randomly allocating the patients to either placebo-control (n = 17) or treatment groups (n = 17). The total study period will be 16 weeks; administration of YKSCH or placebo, as intervention, will be performed for a 12-week period, and follow-up will be performed over a 4-week period. All subjects will undergo conventional treatment, and be required to maintain a regular medication schedule throughout the study period. The primary outcome measure will be the Scales for Outcomes in PD-Sleep Scale score, and the secondary outcome measures will be polysomnography results, findings from instruments related to sleep disorders, neurotransmitter and hormone levels, and hemodynamic changes in the brain cortex.

**Discussion and conclusions::**

This trial will evaluate the effectiveness and safety of YKSCH for sleep improvement in PD with sleep disturbance, and investigate the underlying mechanism of action. We expect improvement in the scores for subjective and objective sleep scales, hemodynamic changes in prefrontal cortical activity, and changes in neurotransmitter and hormone levels. The findings will provide insight into the mechanism underlying the therapeutic effect of YKSCH in PD, and lay the foundation for further studies on whether YKSCH improves sleep disturbance in PD.

**Trial registration number::**

Clinical Research Information Service (KCT0002869).

## Introduction

1

Parkinson's disease (PD) is the second most common progressive neurodegenerative disease and has multiple symptoms.^[1]^ Although PD is clinically defined by its motor features,^[1]^ more than 90% of the patients with PD experience decreased quality of life due to nonmotor symptoms, and the interest in addressing non-motor PD symptoms is increasing.^[2]^ The standard therapy for PD is levodopa, monoamine oxidase (L-DOPA) administration, but it causes several side effects. Most significantly, the long-term use of L-DOPA and dopamine agonists induces motor complications, psychiatric problems, and sleep disturbance.^[3]^ Among the several nonmotor symptoms of PD, sleep disorder is known to be multifactorial,^[4]^ and associations between sleep disturbances and other non-motor symptoms have been reported.^[5,6]^ In addition, studies have demonstrated circadian disturbances in patients with PD exhibiting comorbid sleep disorders, which seem related to changes in cortisol and melatonin hormone levels.^[7,8]^ Recently, doxepin administration and microsubthalamotomy have been reported to be effective therapies against sleep disturbance therapy in PD.^[9,10]^

Yokukansan (YKS) is a traditional medicine that is used for insomnia, night crying in children, and neurosis.^[11]^ Administration of YKS for 8 weeks to patients with dementia is beneficial in terms of sleep disturbance metrics, such as improvement of the sleep disorder inventory score and objective actigraphic evaluations.^[12]^ Mechanistic studies in mice suggest that YKS operates by enhancing pentobarbital-induced sleep involving γ-aminobutyric acid type A (GABA_A_) receptors,^[13]^ and inducing a sleep-promoting effect by causing a decrease in body temperature.^[14]^ However, previous studies on the effect of YKS on sleep disturbance are limited, and mostly focus on neuropsychiatric disorders. Recently, a clinical trial of YKS in PD reported improvement of neuropsychiatric symptoms, such as hallucinations, anxiety, and apathy, using an established Neuropsychiatric Index (NPI).^[3,15]^ A therapeutic role for YKS against psychiatric symptoms is in line with previous findings; YKS attenuated hallucination-like behaviors, such as head-twitch response induced by 2,5-dimethoxy-4iodoamphetamine, and down-regulation of serotonin 5-HT_2A_ receptor density in the prefrontal cortex (PFC) of isolation-stressed mice.^[16]^ In another study, repeated administration of YKS in a restraint-stress rat model led to decreased anxiety-like behavior and stress-induced c-Fos expression in the medial PFC.^[17]^ In addition, anxiolytic effects of YKS were found to involve serotoninergic and dopaminergic transmission.^[18]^

A variant of YKS, called Yokukansankachimpihange (YKSCH), which is a combination of 2 herbs (*Citrus unshiu* peel [Chimpi] and *Pinellia* sp. tuber [Hange]) with YKS,^[19]^ was found to be effective in improving sleep by increasing total sleep time and sleep efficiency of normal healthy adult subjects.^[20]^ In a mouse model of aggressive behavior caused by zinc deficiency, administration of drinking water containing YKSCH decreases aggression by suppressing excessive glutamatergic neuronal activity in the hippocampus.^[19]^ However, only a few studies have evaluated the effects of YKSCH on the improvement of sleep disturbance in PD.

Here, were report the plans for and design of a study that will evaluate the effects of YKSCH on sleep improvement in patients with PD experiencing sleep disturbance. This study will be a prospective, randomized, double-blinded, placebo-controlled, parallel-group pilot trial. The subjects will be patients with PD who are experiencing sleep disturbances, and these subjects will be randomly assigned to a treatment group or control group at a 1:1 ratio. The intervention will be YKSCH administration in the treatment group and placebo administration in the control group. Subjective and objective assessments of sleep improvement will be performed in this study using a questionnaire survey instrument, polysomnography (PSG), and sleep-related hormone measurements. To elucidate the mechanism underlying the effects of YKSCH in PD, hemodynamic changes in the frontal lobe will be measured using functional near-infrared spectroscopy (fNIRS), and the levels of neurotransmitters (NTs) related to PD will also be evaluated.

## Methods and design

2

### Study design and setting

2.1

This study will be a randomized, placebo-controlled trial to identify the efficacy of YKSCH in the treatment of sleep disturbance in PD. During the clinical trial period, all the subjects will be allowed to undergo any combination therapy, such as conventional medicine treatment, non-pharmacotherapy, and exercise therapy, except herbal medicine treatment. In combination therapy, the dosage of anti-PD conventional medication will have to have been stable for at least 1 month prior to enrollment. The primary outcome measure will be the Scales for Outcomes in PD-Sleep Scale (SCOPA-S) score, and the secondary outcome measures will be PSG findings; results of questionnaire survey on non-motor symptoms in PD; changes in NTs and hormone levels, hemodynamic changes in the PFC, as measured by fNIRS in patients with PD. Descriptions of selection of subjects, clinical outcomes, and safety assessment are presented in Table 1. The study setting and site of data collection is the Clinical Trial Center at Dunsan Korean Medical Hospital of Daejeon University in South Korea.

**Table 1 T1:**
[figure not shown]
Schedule for selection of subjects, clinical outcomes, and safety assessment.

### Participants and recruitment

2.2

In total, 34 subjects with PD experiencing sleep disturbance will be recruited through posters placed in the community and hospital, local newspapers, and subway advertisements, from July to October 2018. Subjects who are eligible according to inclusion criteria will provide written informed consent after a consultation, and receive information regarding the clinical study from the coordinator. They will then be randomly allocated to the treatment or control groups.

### Eligibility criteria

2.3

#### Inclusion criteria

2.3.1

A diagnosis of PD made by a neurologist; SCOPA -night score ≧7; Hoehn and Yahr Scale stage 1–4; and provision of informed consent.

#### Exclusion criteria

2.3.2

Patients with Alzheimer's dementia, vascular dementia, Huntington's disease, amyotrophic lateral sclerosis, or hydrocephalus; gait disturbance caused by stroke, brain tumor, or other brain diseases; a diagnosis of gastrointestinal disease, endocrine disease, or cardiovascular disease not controlled by diet or medication; clinical laboratory abnormality, such as serum creatinine ≥97 mmol/L, alanine amino transferase ≥ 40 U/L, aspartate amino transferase ≥ 40 U/L; unstable medical condition, as decided by the research clinician; administration of herbal medication for PD within the last 4 weeks; and inability to undergo fNIRS. Furthermore, patients may be considered ineligible to participate in this clinical study for other reasons, according to the coordinator's discretion

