### Interventions

2.5

Both groups will receive conventional anti-PD medicines, including L-DOPA, dopamine agonists, catechol-*O*-methyl transferase (COMT) inhibitor, and monoamine oxidase (MAO) inhibitor, and will be prohibited from undergoing herbal medicine treatment. We will perform all examinations and assessments in the dopaminergic “on” state (the same time in each patient, after administering the last dose of conventional medication). A constant dose of conventional medication will be maintained during treatment and the follow-up period. If receiving neuropsychiatric drugs, such as sedatives, hypnotics, anxiolytics, selective serotonin uptake inhibitor, and sleep stabilizers, a stable dose of these drugs will have to have been maintained for at least 1 month prior to enrollment. Both YKSCH and placebo drugs will be packed in opaque sachets in granular form to blind researchers and subjects, and will be administered orally 3 times daily. Criteria for discontinuing allocated interventions for subjects are: withdrawal of the clinical trial participation agreement by subjects or their legal representatives, violation of the selection/exclusion criteria during clinical trial, occurrence of adverse events, and less than 70% compliance with medication criteria. To improve adherence to interventions, the *clinical research coordinator will assess medication criteria adherence (number of medicines received/number of medicines to be received)* every time the subjects visit the clinic.

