### Safety assessment and adverse events

2.8

Safety assessment for all subjects will be performed via clinical laboratory examination at baseline, before drug administration; 4 weeks after drug administration (visit 2); and 12 weeks, after completing drug administrations (visit 4). Laboratory tests will include those for live rand renal function, which can possibly be damaged by herbal medicines,^[2]^ and serum potassium concentration because *Glycyrrhiza radix*, a component of YKSCH, can induce hypokalemia.^[3]^ Adverse events will be defined as undesirable and/or unexpected medical findings which did not occur before the start of this clinical trial, and will be recorded, regardless of their relation to YKSCH or the placebo drug. The severity of the adverse events will be evaluated based on the step-wise criteria established by the chief investigator, and reported to the IRB of Daejeon University. Following appropriate deliberation, the IRB will determine whether the trial should be discontinued. Causal link between the adverse events and the procedure will be investigated by the doctor-in-charge, and categorized into 6 stages based on the aforementioned evaluation criteria. In case of a severe adverse event, appropriate treatment and follow-up will be provided.

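### The printed creatinine exclusion limit of 97 mmol/L cannot be met by any patient, so this numeric threshold excludes nobody

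*Protocol article*

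**What the plan says.** Section 2.3.2 (Exclusion criteria) of the Protocol article excludes patients with a "clinical laboratory abnormality, such as serum creatinine ≥97 mmol/L, alanine amino transferase ≥ 40 U/L, aspartate amino transferase ≥ 40 U/L". The creatinine figure, "serum creatinine ≥97 mmol/L", is the only quantified renal criterion in the available text, and no other section gives a creatinine limit or a different unit.

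The same section has two open-ended routes to exclusion: "unstable medical condition, as decided by the research clinician", and a closing sentence under which "patients may be considered ineligible to participate in this clinical study for other reasons, according to the coordinator's discretion".

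Two other sections bear on the point. Section 2.8 (Safety assessment and adverse events) schedules laboratory tests at baseline, visit 2 and visit 4, and includes "renal function, which can possibly be damaged by herbal medicines" among the reasons for them. Section 2.5 (Interventions) lists "violation of the selection/exclusion criteria during clinical trial" among the grounds for stopping the allocated intervention.

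**The concern.** A concentration of 97 mmol/L is out of scale for serum creatinine. The two liver enzyme limits beside it, each 40 U/L, are values that a laboratory report could plausibly show; the creatinine limit is not. A threshold that no result can reach does no work: applied literally, every candidate passes it, whatever the state of their kidneys.

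That matters more here than in most trials, because the article itself regards renal function as something the study treatment might harm. Staff who notice the problem have to supply their own reading of the limit. Who is eligible on renal grounds then depends on an unwritten decision and not on the protocol. If the exclusion criteria are also re-applied during treatment, which is one way to read section 2.5, the same threshold fails there too.

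**Working it through.** The article gives no derivation of the figure 97, so there is nothing to reproduce. The check is a unit conversion.

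**Inputs**
- Limit: 97 mmol/L (section 2.3.2).
- Molar mass of creatinine: 113.12 g/mol. This is a chemical constant and is not in the article.
- Serum creatinine in extreme renal failure: 1,000 to 3,000 µmol/L. This is an assumption, used only for scale.

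**Step 1. The limit as printed**
- g/L = mmol/L × molar mass / 1,000: 97 × 113.12 / 1,000 = 10.97 g/L.
- mg/dL = mmol/L × molar mass / 10: 97 × 113.12 / 10 = 1,097 mg/dL.
- µmol/L = mmol/L × 1,000: 97 × 1,000 = 97,000 µmol/L.

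**Step 2. Distance from any attainable value**

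| Assumed extreme value (µmol/L) | Printed limit / assumed value |
|---|---|
| 1,000 | 97,000 / 1,000 = 97 |
| 2,000 | 97,000 / 2,000 = 48.5 |
| 3,000 | 97,000 / 3,000 = 32.3 |

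Even at the top of the assumed range, the limit is about 32 times too high to be reached. The conclusion does not depend on where in that range the true extreme lies.

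**Step 3. The same number in other units**
- In µmol/L: 0.097 mmol/L × 113.12 / 10 = 1.10 mg/dL. The ratio to the printed limit is 1,097 / 1.097 = 1,000.
- In mg/L: 97 / 10 = 9.7 mg/dL. This too is attainable, in severe renal failure.

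A slip between milli and micro is the likeliest explanation, since it turns the figure into an ordinary laboratory magnitude. It is not the only unit in which 97 is attainable, so the text alone does not settle what was meant.

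**Step 4. What else could exclude or flag the patient**

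The three laboratory values are introduced as examples, so the excluded condition is the abnormality itself. A clearly abnormal creatinine can still be excluded under that wording, as an unstable condition judged by the clinician, or at the coordinator's discretion. None of these routes gives a number.

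**The case against.** A reader might infer that no patient with renal impairment can ever be excluded or flagged. The article does not support that. The laboratory limits are illustrative, and section 2.3.2 leaves room for judgement and discretion. Section 2.8 tests renal function in all subjects at baseline and twice afterwards, section 2.5 makes adverse events a separate ground for stopping, and section 2.10 provides an independent monitoring committee. This objection stands and confines the point to the printed number.

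A reader might also infer that different sites will apply different limits. Section 2.1 names a single centre, whose staff may well notice a figure so far out of scale. That lowers the practical risk, but relying on staff to correct a criterion silently is no substitute for a correct criterion.

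The link to stopping treatment is likewise only one reading. The phrase in section 2.5 may mean ineligibility discovered after entry, and need not mean that each screening limit is re-applied at each visit.

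Finally, the article condenses a fuller protocol (version 1.1, section 2.11), and the slip may have arisen in typesetting or text extraction. Other special characters, such as γ, ≥ and °, came through intact, which makes extraction less likely as the cause. No µ appears anywhere in the text, so this cannot be tested directly. Whether the working protocol carries the same error is unknown. The printed article does, and a condensed account may leave things out but should not state an impossible value.

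**Conclusion.** The point holds for the printed threshold. The only numeric renal exclusion in the article equals about 1,097 mg/dL, roughly 32 to 97 times any value assumed for extreme renal failure, and excludes nobody. This rests on the molar mass of creatinine and on the unit as printed; the assumed range serves only for scale.

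The consequence is limited. Renal impairment can still lead to exclusion through the general wording, clinician judgement or discretion, and renal function is monitored. The threshold is inoperative during treatment only if section 2.5 is read as re-applying the exclusion criteria. A factor of 1,000 is the size of the error if the intended unit was µmol/L, which is likely but unproven.

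The 34-subject sample size, the 80% power, the 5% significance level and the planned analyses are not affected. It is a safety-related eligibility value that is wrong as written and cheap to correct.

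**What to change.** Check the value and unit in section 2.3.2 against the full protocol and against the unit in which the trial laboratory reports creatinine. Have the investigator confirm the intended limit; this review does not propose one. Then correct the entry wherever it was copied: protocol, case report form and registry record. State at the same time whether the ground in section 2.5 covers laboratory limits re-applied during treatment or only ineligibility discovered after entry, so that the two sections can be read together.

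The cost is a short text correction, with notice to the ethics board and registry if those documents carry the error. It should be done before screening, since section 2.2 plans recruitment from July 2018. A corrected limit may exclude some candidates whom the printed one lets through; the article gives no creatinine distribution from which to estimate how many. No statistical work has to be redone.

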##### Scales for outcomes in PD-sleep scale

2.6.1.1

The score of SCOPA-S, which is a questionnaire survey assessing problems in both night- and day-time sleep, and the measurement of PD^[4,9,21]^ the severity will be the primary outcomes measured in this study. The survey will be conducted at baseline (visit 1) and 12 weeks after treatment (visit 4) for both groups.

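### The pre-entry herbal exclusion covers only herbs taken for PD, while the in-trial ban covers all herbal medicine, so some patients may enter with a herb-treated baseline

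*Protocol article*

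**What the plan says.** Section 2.3.2 (Exclusion criteria) limits the pre-entry rule on herbs by indication: it excludes "administration of herbal medication for PD within the last 4 weeks". The in-trial rules carry no such limit. Section 2.1 allows combination therapy "such as conventional medicine treatment, non-pharmacotherapy, and exercise therapy, except herbal medicine treatment", and section 2.5 says that both groups "will be prohibited from undergoing herbal medicine treatment".

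The Introduction describes the formula from which the study product derives: "Yokukansan (YKS) is a traditional medicine that is used for insomnia, night crying in children, and neurosis".

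Three other provisions bear on the point:
- Section 2.3.1 sets the sleep entry threshold as "SCOPA -night score ≧7" and does not say that the score must be taken off herbs.
- Section 2.6.1.1 fixes the timing of the primary outcome: "The survey will be conducted at baseline (visit 1) and 12 weeks after treatment (visit 4) for both groups".
- Section 2.9.2 compares the before-after difference in SCOPA-S between groups by a two-sample t-test or Mann–Whitney test. PSG and hormone measures are compared before and after treatment by paired tests.

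**The concern.** The rule before entry and the rule during the trial differ in scope. The gap falls on the symptom under study: a patient with disturbed sleep who used a herbal remedy would plausibly have taken it for insomnia, and the words on PD need not reach that use. The site is a Korean medicine hospital that recruits partly through hospital posters, so prior herbal users are plausible, although the article does not say how many there are.

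For such a patient the visit 1 score may already contain the benefit of the study product or a relative of it. If allocated to YKSCH, the patient replaces one herb with a similar one and changes little. If allocated to placebo, the patient may worsen as the earlier effect wears off. Neither change answers whether adding YKSCH improves sleep. At stake are the meaning of the primary change score in these patients, some precision, and the paired PSG and hormone tests, which make no comparison between arms and so get no protection from randomisation.

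**Working it through.** **Step 1: the text.**

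| Rule | Section | Period | Limited to herbs for PD? |
|---|---|---|---|
| Herbal exclusion | 2.3.2 | 4 weeks before entry | Yes |
| Herbal ban | 2.1 | During the trial | No |
| Herbal ban | 2.5 | During the trial | No |

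Two other clauses could close the gap, and neither does.
- The rule in 2.5 for neuropsychiatric and sleep drugs asks that "a stable dose of these drugs will have to have been maintained for at least 1 month prior to enrollment". Its list of drug classes does not name herbal products. If it were stretched to cover them, it would call for a stable dose and so clash with the in-trial ban.
- The closing clause of 2.3.2 says that "patients may be considered ineligible to participate in this clinical study for other reasons, according to the coordinator's discretion". This permits exclusion of a recent herb user but does not require it.

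**Step 2: the planned effect size.** Section 2.9.1 gives 34 patients (17 per group), 10% dropout, two-sided 5% and 80% power, but prints no effect size or SD, so the 34 cannot be reproduced directly. Working backwards:
- Evaluable per arm: 15 / 0.9 = 16.7, rounded up to 17. So 15 evaluable per arm fits the plan.
- Normal approximation: d = (1.96 + 0.84) × √(2/15) = 1.02.
- Noncentral t with 28 degrees of freedom and 80% power: d = 1.06. This value is used below.

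**Step 3: effect on the primary comparison.** Let q be the share of enrolled patients with a herb-treated baseline (assumed). Suppose the earlier herb works as well as YKSCH and its effect has worn off by week 12 if it is not continued. Mean improvement, in SD units, is then:

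| | YKSCH | Placebo |
|---|---|---|
| No prior herb (1 − q) | d | 0 |
| Prior herb (q) | 0 | −d |
| Arm mean | (1 − q)d | −qd |

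The difference between arms is (1 − q)d + qd = d, which is unchanged. Each arm is now a mixture, so its variance rises from 1 to 1 + q(1 − q)d². The standardised difference becomes d / √(1 + q(1 − q)d²), with d² = 1.06² = 1.1236.

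| q (assumed) | Variance factor | Standardised difference | Power, 15 per arm |
|---|---|---|---|
| 0% | 1.00 | 1.06 | 80% |
| 5% | 1 + 0.0475 × 1.1236 = 1.05 | 1.033 | 78% |
| 10% | 1 + 0.09 × 1.1236 = 1.10 | 1.010 | 76% |
| 20% | 1 + 0.16 × 1.1236 = 1.18 | 0.976 | 73% |

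**Step 4: effect on the paired tests.** Under the same assumptions, the arm means in Step 3 are what a paired test sees. With an effect D on a given PSG or hormone measure, the YKSCH arm shows (1 − q)D instead of D, and the placebo arm shows −qD instead of 0. At q = 10% that is 0.9D and −0.1D. These are shifts in the mean, not only a loss of precision.

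**The case against.** **The wording can be read more broadly.** The Discussion treats sleep disturbance as a non-motor symptom of PD, so a herb for PD-related insomnia could count as a herb for PD. That reading is fair and would narrow the gap. It is not stated, though, and it would still leave out herbs taken for insomnia unrelated to PD or for other complaints.

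**The full protocol may say more.** The article condenses a longer document, and Table 1 could not be read for this check. But the criterion is printed here with an explicit limit, and it does not match the ban printed in the same article.

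**A reader might infer that prior users stop their herb at randomisation.** The article does not say so. Section 2.1 speaks only of the trial period, and the stopping time relative to visit 1 is not given. A treated baseline is therefore possible but not established.

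**A reader might infer a biased treatment comparison or a severe loss of power.** Neither is supported. Randomisation balances prior use in expectation, and in the reversible case the mean difference is kept. A much larger loss would need, for example, an earlier herb effect that persists through week 12. Nothing in the article supports that, and a 4-week exclusion would not cure it. Chance imbalance in prior use is not a further harm to the t-test, because the variance already reflects it.

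**Cost and benefit rise together.** If prior users are few, the power loss is one or two points. If they are many, excluding or delaying them costs recruitment at a single site that plans to enrol 34 patients from July to October 2018. This stands, and it keeps the point minor.

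**Conclusion.** The mismatch in scope is real on the printed text, and no other provision closes it. Its consequence is limited. The primary contrast is not biased in expectation. Power falls from 80% to about 78%, 76% or 73% for an assumed 5%, 10% or 20% of prior users. Those figures rest on three assumptions: a prior-user share that the article does not give; 15 evaluable patients per arm; and a reversible herb effect equal to d = 1.06, which is back-solved from a sample size based on a doxepin study rather than on any YKS effect. A smaller herb effect would cost less. The clearer gains from aligning the rules are in interpretation: a baseline for the primary change score that is free of recent herbal treatment, and paired PSG and hormone tests that are not shifted. This is a minor, cheap improvement, not a threat to the trial's validity.

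**What to change.** Reconcile sections 2.1, 2.3.2 and 2.5 so that the pre-entry herbal exclusion has the same any-indication scope as the in-trial ban, within the window that the protocol already uses. In 2.3.2 this means removing the restriction to PD; no new duration is introduced. Add a screening question on prior herbal use (product, reason, date last taken) and record the answer at baseline, so that any remaining effect can be described.

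The cost is one phrase and one case report form item. The downside is that some candidates would be delayed or excluded, which may slow recruitment at this single Korean medicine site. If the sponsor already intends herbs for PD-related insomnia to count as herbs for PD, saying so would close part of the gap, but not the part that concerns herbs for other reasons.
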